### ***Inflammation and Sanfilippo Syndrome***

Neurologic and somatic inflammation have been implicated in disease pathogenesis in the MPS disorders. For Sanfilippo syndrome, elevation in levels of interleukin-1 $\alpha$  (IL-1 $\alpha$ ) and monocyte chemoattractant protein-1 (MCP-1) have been reported in the MPS IIIB mouse model in both brain and plasma. Despite less visually obvious somatic sequelae compared to other forms of MPS, patients with Sanfilippo syndrome experienced the highest frequency of pain in a Dutch national survey as measured by the Non-communicating Children's Pain Checklist-Revised (NCCPC-R). It is widely understood that inflammation is a source of pain and due to the known inflammatory nature of accumulated GAG fragments, addressing inflammation is a rational approach to improving quality of life. Thus, adjunctive therapies aimed at decreasing inflammation are currently being studied in many MPS disorders and benefits in both somatic and CNS disease have been reported. For example, treatment with prednisolone alone has been shown to correct behaviors in MPS IIIB mice, and inhibition of IL-1 through gene therapy-induced overexpression of the human IL-1 receptor antagonist (IL-1Ra) results in a reduction in the number of activated microglia and astrogliosis, and significant improvements in hyperactivity and working memory in MPS IIIA mice. These studies provide the rationale for testing the effects of anakinra, an IL-1 receptor antagonist, in children with MPS III.

**We hypothesize that anakinra will reduce hyperactivity and irritability, as well as improve sleep, in children with MPS III.**

## **5.0 Inclusion and Exclusion Criteria**

### ***5.1 How participants will be screened***

Potential participants will be pre-screened by phone or email with the following questions:

1. *Does your child have sleep problems that make him or her get less sleep than needed? Y/N*
2. *Does your child have challenging behaviors that make it difficult to go on outings or manage the child's daily needs? Y/N*
3. *Does your child have pain or unexplained episodes of distress? Y/N*
4. *Does your child have seizures or movement disorders? Y/N*
5. *Does your child have more difficulty than a same-aged healthy child walking and getting around independently? Y/N*
6. *Does your child require more supervision than a same-aged healthy child to keep them safe? Y/N*

***If in the opinion of the investigator, the patient may be a candidate for an enzyme restorative trial that is enrolling participants, the caregiver will be directed to information on that trial(s) at [clinicaltrials.gov](https://clinicaltrials.gov). This will also be assessed at the screening visit using the inclusion criteria described below which are in part based on exclusion criteria from currently active enzyme restorative trials.***

If the answer to 2 or more of these is “yes”, then we will schedule a screening visit at our center. Disease burden in these areas will be confirmed through the protocol specified outcome measures.

At the Screening visit consent and assent forms will be reviewed in detail and the patient and their parents/legal guardians will have the opportunity to ask any questions they may have. The parents will also be asked to describe the protocol prior to signing these forms to ensure that all details are clearly understood. Screening evaluations will then be performed as detailed in Table 1.

## **5.2 Inclusion criteria**

- MPS III diagnosis confirmed by genetic testing.
- $\geq 4$  years of age.
- Patient or parent/legal guardian is able and willing to provide informed consent. For patients 7 to 17 years of age, assent must also be provided when cognitively possible.
- If on Genistein, must have been on a stable dose for 6 months prior to enrollment.
- If on melatonin or other sleep medications, must have been on stable doses for the past 3 months.

- Two of the following criteria are met:
    1. CSHQ Total score  $\geq 41$ .
    2. SBRS Cluster or Domain score  $\geq -2$  SD of mean for age group.
    3. The presence of significant MPS III related CNS impairment or behavioral disturbances.
    4. NCCPC-R Total Score of  $\geq 7$ .
  - 5. Seizure disorder thought to be due to MPS III related disease changes, requiring use of regular medication.
  - 6. Presence of a movement disorder.
- OR**, one of the following criteria are met:
1. Previous participation in a gene/cell therapy or enzyme restorative clinical trial.
  2. Previous rejection from a gene/cell therapy or enzyme restorative clinical trial.
  3. Functional age as measured by the Vineland is  $\leq 0.5$  chronological age.

### 5.3 Exclusion

- Currently enrolled in another ongoing clinical treatment trial.
- Previous or current treatment with anakinra, canakinumab or any other IL-1 inhibitor.
- Use of the following therapies prior to enrollment:
  - ☐ Narcotic analgesics within 24 hours prior to enrollment.
  - ☐ Tocilizumab, dapsone or mycophenolate mofetil within 3 weeks prior to enrollment.
  - ☐ Etanercept, leflunomide, thalidomide, or cyclosporine or intraarticular, intramuscular, intravenous, or oral administration of glucocorticoids within 4 weeks prior to enrollment.
  - ☐ Intravenous immunoglobulin (IVIG), adalimumab, or methotrexate within 8 weeks prior to enrollment.
  - ☐ Infliximab, 6-mercaptopurine, azathioprine, cyclophosphamide or chlorambucil within 12 weeks prior to enrollment.
  - ☐ Rituximab within 26 weeks prior to enrollment.
- Live vaccines within 1 month prior to enrollment.
- Known presence or suspicion of active, chronic or recurrent serious bacterial, fungal or viral infections, including tuberculosis, HIV infection or hepatitis B or C infection.
- Clinical evidence of liver disease or liver injury as indicated by presence of abnormal liver tests.

- ☐ AST or ALT > 5 x ULN, or
- ☐ AST or ALT > 3 x ULN accompanied by elevated bilirubin >2 x ULN.
- Presence of severe renal function impairment (estimated creatinine clearance < 30 mL/min/1.73m^2).
- Presence of neutropenia (defined as ANC <1200 cells/microliter).
- History of malignancy.
  
- Known hypersensitivity to *E. coli*-derived proteins, or any components of Kineret™ (anakinra).
- Pregnant or lactating women.
- Current active infection.
- History of serious opportunistic infection (e.g. bacterial [Legionella and Listeria]; tuberculosis [TB]; invasive fungal infections; or viral, parasitic, and other opportunistic infections).
- Positive TB skin test, positive Quantiferon-TB Gold TB test, positive chest x-ray, or a recent exposure to TB.
- Requirement for live vaccine exposure that would be expected to occur during the time frame of the study.
- Any other social or medical condition that the Investigator believes would pose a significant hazard to the subject if the investigational therapy were initiated or be detrimental to the study.

#### **5.4 Special populations**

- ☐ Adults unable to consent will be included.
- ☐ Individuals who are not yet adults (infants, children, teenagers) will be included.
- ☐ Pregnant women will not be included.
- ☐ Prisoners will not be included.

### **6.0 Study-Wide Number of Subjects**

Twenty (20) subjects will be enrolled in this pilot study. Individuals who withdraw before Week +8 will be replaced.

### **7.0 Study-Wide Recruitment Methods**

Potential subjects will be recruited through study physicians' and other MPS physicians' clinical practices. The study will be registered on clinicaltrials.gov. Information on the study will be shared through social media as well.

## 8.0 Study Timelines

- The duration of an individual subject's participation in the study will be 52 weeks.
- The duration anticipated to enroll all study subjects is 1 year.
- The estimated date for the investigators to complete this study (complete primary analyses) is 3 months after the last subject's Week +8 visit.

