## 9.0 Study Endpoints

### 9.1 Primary and secondary endpoints.

#### Primary endpoints:

Phase 1: Incidence of treatment-emergent adverse events and laboratory values over 8 weeks of treatment to known frequency of anakinra-related AEs in other populations.

Phase 2: Need for dose escalation as determined by within individual change over 8-week treatment period compared to change over 8-week observational period in the 2 most bothersome symptoms for each enrolled patient, selected from measures for the MDRI. Choices are below in bold. These 2 symptoms will be monitored by one or more of the assessments below. If the Minimal Clinically Important Difference (MCID) that is defined below is not achieved after 8 weeks of treatment, or there has been a decrease of more than the MCID between 8 and 16 weeks after an increase greater than MCID at week 8, the dose will be escalated (see Section 27.7). If the MCID is not achieved after 8 weeks on maximum trial dose of 200mg (max dose 8 mg/kg/day), treatment with anakinra may be discontinued (see Section 27.7).

- Sanfilippo **Behavior** Rating Scale (SBRS): MCID = 0.25 SD for each scale
  - Symptoms described in table below:

|                         |                                                                                                                                        |                           |
|-------------------------|----------------------------------------------------------------------------------------------------------------------------------------|---------------------------|
| Body Movements          | Makes large complex movements of their body, such as spinning, twirling or repeatedly bouncing up and down.                            | Movement                  |
| Object Interaction      | Examines or manipulates some novel or unfamiliar objects repeatedly.                                                                   |                           |
| Activity/Routines       | Never plays with one object or engages in one activity for very long.                                                                  |                           |
| Emotional Function      | Expresses emotions inappropriate to the situation.                                                                                     | Social/emotional function |

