## 12.0 Data Management and Confidentiality

### 12.1 Subject Population(s) for Analysis

- ☐ Protocol-compliant population (PP): Any subject who received at least 85% of planned doses and attended all scheduled study visits.
- ☐ Safety population (SP): All subjects who receive any amount of treatment.

Safety population (SP) will be used for the primary analyses and the secondary analysis would be based on protocol-compliant population (PP) as part of sensitivity analyses.

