**3. Frequency of review, and rationale for recommended frequency.**

Frequency of Review: Every 6 months .

Rationale for Review Frequency: Limited number of subjects in the study (20 will be enrolled over 24 months) and the level of moderate risk.

**4. Designation of individual(s) as independent monitor(s) reviewing the information. An explicit review of any conflict of interest issues should be presented.**

[name] will act as the Monitor for this clinical study. [name] is a faculty member at the University of Minnesota with an appointment in the Department of Pediatrics, Division of Rheumatology. He is the Director of the Division of Pediatric Rheumatology. He has been a site Investigator for multiple clinical trials for juvenile idiopathic arthritis and other autoinflammatory diseases, including a study of anakinra. He has been a member of multiple DSMB for the NIH. In addition, he has expertise in the clinical use of anakinra.

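### One whole-study protocol-compliant definition is also applied to the 8-week primary endpoints, so their sensitivity analysis selects children on dosing and attendance after the endpoint is measured

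*Protocol*

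**What the plan says.** **Analysis sets (Protocol 12.1).** The protocol-compliant population is "Any subject who received at least 85% of planned doses and attended all scheduled study visits". No separate version is given for any endpoint. On use, "Safety population (SP) will be used for the primary analyses", whereas "the secondary analysis would be based on protocol-compliant population (PP) as part of sensitivity analyses".

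**Primary endpoints (9.1).** Phase 1 is adverse events and laboratory values over 8 weeks of treatment. Phase 2 is the need for dose escalation, judged from within-child change over the 8-week treatment period against the 8-week observation period. It has a later component, where "there has been a decrease of more than the MCID between 8 and 16 weeks after an increase greater than MCID at week 8".

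**Length of follow-up (8.0, 10.1, 10.2).** Each child has 8 weeks of observation, 36 weeks of treatment and 8 weeks off treatment. The last visit is Week +44.

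**Timing (8.0).** "The estimated date for the investigators to complete this study (complete primary analyses) is 3 months after the last subject's Week +8 visit".

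**Stopping of drug (14.0, 27.7).** If the MCID is not reached after 8 weeks on the maximum trial dose, treatment may be discontinued after discussion with the parents. Drug is also stopped for listed liver findings, serious infection, malignancy, severe hypersensitivity, and listed adverse events that do not resolve after dose reduction.

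**The concern.** A per-protocol set should be defined over the window in which its endpoint is measured. Here membership for an 8-week result depends on what happens up to Week +44. That alone is conditioning on the future. It becomes a bias if the later events depend on the 8-week result, and in this protocol some of them do: early non-response leads to escalation and possibly to discontinuation, and adverse events lead to stopping.

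The PP set can therefore lose non-responders and children with adverse events. There are 20 children and no control arm, so a sensitivity analysis that agrees with the primary result, or looks better, could be taken as reassurance when part of the agreement comes from the selection rule.

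**Working it through.** **1. Calendar.** The stated participation reproduces: 8 + 36 + 8 = 52 weeks. The primary window ends at Week +8. PP membership is settled only at Week +44, which is 44 − 8 = 36 weeks later.

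**2. Does the dosing criterion reach past Week +8?** Take one dose a day over the 36-week treatment period:
- Planned doses: 36 × 7 = 252.
- Threshold: 0.85 × 252 = 214.2, so 215 doses.
- Earliest time to reach it: 215 / 7 = 30.7 weeks, about Week +31.

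A child with perfect dosing to Week +8 has 56 / 252 = 22% of planned doses, so nearly all of the qualifying doses come after the endpoint.

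**3. Does the protocol link later dosing to the early result?** Under 27.7:
- A child escalated at Week +8 who does not reach the MCID may be stopped at Week +16: 112 / 252 = 44%, fails PP.
- A child escalated at Week +16 who does not reach the MCID may be stopped at Week +24: 168 / 252 = 67%, fails PP.

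Both are exclusions caused by poor response. Stopping for adverse events under 14.0 or 27.7 before about Week +31 has the same effect.

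**4. How large could the shift be?** The documents give no retention rates, so this is an illustration. Take a normally distributed 8-week change with true mean 0, split at its median. The two halves have means of ±0.798 SD. With retention in PP of *a* above and *b* below the median, the PP mean is 0.798 × (a − b) / (a + b).

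| Assumed a | Assumed b | PP mean change |
|---|---|---|
| 0.9 | 0.7 | 0.798 × 0.2 / 1.6 = +0.10 SD |
| 0.9 | 0.6 | 0.798 × 0.3 / 1.5 = +0.16 SD |

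**5. Secondary consequence for timing.** Three months is about 13 weeks, so the 8.0 date falls at about 8 + 13 = Week +21 of the last child, 44 − 21 = 23 weeks before that child's last visit. Section 6.0 states "Twenty (20) subjects will be enrolled in this pilot study". The accrual pattern is not stated; assume it is uniform.
- Section 8.0, "The duration anticipated to enroll all study subjects is 1 year": 20 × 23 / 52 = 8.85, about 9 children not yet at Week +44.
- Appendix A, "20 will be enrolled over 24 months": 20 × 23 / 104 = 4.4, about 4 to 5 children.

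Taking 3 months as 12 weeks changes the first figure only to 9.2. If PP were limited to the 8-week window, the number would be 0 under either enrolment period.

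**The case against.** - **The primary result is untouched.** It uses the safety population, which needs only some treatment, so no treated child is lost. This stands, and it limits the importance of the point.
- **Endpoint-specific sets belong in an analysis plan.** That would answer a silent protocol. This protocol is not silent: 12.1 fixes one definition and assigns its use.
- **The shift is small and assumed.** Even +0.16 SD is below the margin of error of about half an SD given in 12.3, and the retention rates have no source in the documents. Both statements are right. The direction comes from the stopping rules; the size does not.
- **Children who stop drug are asked to stay in follow-up (14.0).** This limits missed visits but does nothing for the 85% dosing criterion.
- **Discontinuation is discretionary, and planned doses might mean doses planned up to stopping.** On that reading a child stopped under the protocol could remain compliant. The text does not say so, and a definition should not depend on it.
- **The PP set might be meant only for the secondary endpoints.** It is described as a sensitivity analysis directly after the primary set, so a second look at the primary outcomes is the natural reading. Several secondary endpoints also use an 8-week change.

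A reader might infer two stronger points. The first is that about 9 of 20 children cannot qualify for PP in time. Section 8.0 dates only the primary analyses, and nothing requires PP results by then. The figure also needs uniform accrual over one year, and it means status not yet known rather than exclusion. The second is that late enrollees would lack their Week +16 assessment. That requires a data cut at Week +8, which the protocol does not set; at about Week +21 every child still in the study has passed Week +16.

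**Conclusion.** The point holds for the PP definition. A set that requires 215 of 252 doses and every visit to Week +44 is not suitable for a sensitivity analysis of 8-week endpoints, because the protocol's own stopping provisions can remove children for poor response or adverse events after the endpoint is measured. The likely direction is towards a more favourable result.

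The size cannot be derived from the documents. The range of +0.10 to +0.16 SD rests on assumed retention of 90% above and 60 to 70% below the median. The safety-population analysis does not change. Open PP status for about 4 to 9 of 20 children at the Section 8.0 date is a side effect that rests on uniform accrual and on which of the two enrolment periods applies. It is not a conflict with the timetable. This is a modest defect in a sensitivity analysis, worth correcting because the correction costs almost nothing.

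**What to change.** In 12.1, define PP for the 8-week primary endpoints over their own window:
- the 85% dosing threshold counted from Day 1 to Week +8 only (0.85 × 56 = 47.6, so 48 of 56 daily doses);
- completion of the Week -8, Day +1, Week +2, Week +4 and Week +8 assessments. Weeks +2 and +4 are needed because their safety laboratory tests feed the Phase 1 endpoint;
- Week +16 attendance added only for the Week +16 escalation component of Phase 2.

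Keep the full-length definition for the Week +36 and Week +44 endpoints. Reconcile the enrolment periods in 8.0 and Appendix A.

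The cost is a few sentences and a second PP flag to derive, with no new data. A window-matched set still excludes children who stop early within the first 8 weeks, so for adverse events the safety population should remain the set that is relied on.

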## 9.0 Study Endpoints

### 9.1 Primary and secondary endpoints.

#### Primary endpoints:

Phase 1: Incidence of treatment-emergent adverse events and laboratory values over 8 weeks of treatment to known frequency of anakinra-related AEs in other populations.

Phase 2: Need for dose escalation as determined by within individual change over 8-week treatment period compared to change over 8-week observational period in the 2 most bothersome symptoms for each enrolled patient, selected from measures for the MDRI. Choices are below in bold. These 2 symptoms will be monitored by one or more of the assessments below. If the Minimal Clinically Important Difference (MCID) that is defined below is not achieved after 8 weeks of treatment, or there has been a decrease of more than the MCID between 8 and 16 weeks after an increase greater than MCID at week 8, the dose will be escalated (see Section 27.7). If the MCID is not achieved after 8 weeks on maximum trial dose of 200mg (max dose 8 mg/kg/day), treatment with anakinra may be discontinued (see Section 27.7).

- Sanfilippo **Behavior** Rating Scale (SBRS): MCID = 0.25 SD for each scale
  - Symptoms described in table below:

|                         |                                                                                                                                        |                           |
|-------------------------|----------------------------------------------------------------------------------------------------------------------------------------|---------------------------|
| Body Movements          | Makes large complex movements of their body, such as spinning, twirling or repeatedly bouncing up and down.                            | Movement                  |
| Object Interaction      | Examines or manipulates some novel or unfamiliar objects repeatedly.                                                                   |                           |
| Activity/Routines       | Never plays with one object or engages in one activity for very long.                                                                  |                           |
| Emotional Function      | Expresses emotions inappropriate to the situation.                                                                                     | Social/emotional function |
| Eye Contact             | Makes effort to avoid other people's gaze (keeps head down, looks away, or turns away).                                                |                           |
| Social Interaction      | Participates in group activities.                                                                                                      |                           |
| Emotional Engagement    | Doesn't seem to recognize or respond to other people's emotion.                                                                        |                           |
| Comfort Seeking         | Actively seeks comfort from familiar people.                                                                                           | Lack of Fear              |
| Safety Consciousness    | Is less aware of danger around the house (e.g. would touch hot oven) on the street or in the playground than other children their age. |                           |
| Fearfulness             | Is less fearful of new strange or scary things than other children of same age.                                                        |                           |
| Attention               | Is easily distracted                                                                                                                   | Executive function        |
| Self-Control/Compliance | Is impulsive, can't stop self.                                                                                                         |                           |
|                         |                                                                                                                                        |                           |
| Orality                 | Puts everything in their mouth; eats inedible things.                                                                                  |                           |
| Mood/Anger/Aggression   | Mood is irritable and cranky.                                                                                                          |                           |
| Self-Gratification      | Rubs genitals with hands, inside or outside clothing                                                                                   |                           |

- Child **Sleep** Health Questionnaire (CSHQ): MCID = 1-point change on the CSHQ Total score 
- Autism **Parenting Stress** Index (APSI): MCID = 0.25 SD for Stress Total 
  - Ability to communicate
  - Tantrums/meltdowns
  - Self-injurious behavior
  - Difficulty making transitions from one activity to another
  - Toilet training
  - Not feeling close to your child
  - Concern for your child not being accepted by others
  - Concern for the future for your child living independently
- PROMIS **Fatigue** - Parent Proxy Custom Short Form: MCID = 3-point change
- **Seizures** – Parents will record each seizure in a seizure journal provided by the study. Information recorded will include the duration (average length of seizure), and need for medical intervention (e.g. rescue medication, medical evaluation).

- **Movement** disorder (e.g. dystonia, chorea, etc.) – Parent reported duration and severity. Change in one of two characteristics for +/-1 score, +/-2 score for change in two of the characteristics.
- Non-communicating Children's **Pain** Checklist-Revised (NCCPC-R): MCID = 0.25 SD

